## Abstract

**Background:**

Mild cognitive impairment (MCI) is a syndrome characterised by a decline in cognition but relatively intact activities of daily living. People with MCI have an increased risk of developing dementia, and MCI is often referred to as a transitional stage between healthy ageing and dementia. Currently, there are no pharmaceutical therapies approved by the US Federal Drug Administration for MCI. Randomised controlled trials on the two major classes of anti-dementia pharmaceuticals, cholinesterase inhibitors and glutamate receptor antagonists, have produced poor results in MCI cohorts. There is a need to test and evaluate new and promising treatments for MCI that target multiple aspects of the syndrome’s multi-faceted pathophysiology. The primary aim of this study is to evaluate the efficacy of 12 weeks of treatment with a standardised herbal formula, Sailuotong (SLT), compared to placebo, on cognition in older adults with MCI. Secondary aims are to assess SLT’s mechanisms of action via electroencephalography (EEG), autonomic function, brain blood flow, and inflammation, as well as its safety in this cohort.

**Methods/design:**

The target cohort for this trial is community-dwelling older adults over the age of 60 years who meet the National Institute of Aging-Alzheimer’s Association working group core clinical criteria for MCI due to Alzheimer’s disease. Eighty participants will be recruited and randomly allocated via a permuted block strategy at a 1:1 ratio to either the treatment or placebo group. The co-primary cognitive outcome measures are Logical Memory Story A delayed recall (episodic memory), Letter Number Sequencing (perceptual processing speed), and both the Trail Making Test and Rey Complex Figure Test (executive function). Secondary outcome measures are EEG activity, autonomic function (via electrocardiogram, skin conductance, and peripheral pulse pressure), brain blood flow (via common carotid artery ultrasound), and serum concentrations of inflammatory cytokines. Analyses will be performed blind to group allocation.

**Discussion:**

This study is a 12-week, randomised, double-blind, placebo-controlled trial. Primary and secondary outcome measures will be compared between treatment and placebo groups at baseline and endpoint. Data from this pilot study will inform a larger, more highly powered clinical trial if the findings are positive.

**Trial registration:**

Australian New Zealand Clinical Trials Registry (ANZCTR), ACTRN12617000371392 Registered on 10 March 2017.

**Electronic supplementary material:**

The online version of this article (10.1186/s13063-018-2912-0) contains supplementary material, which is available to authorized users.

## Background

### Overview

Mild cognitive impairment (MCI) causes a slight but noticeable decline in cognitive abilities and is conceptualised as a transitional stage between healthy ageing and dementia. It is estimated that up to 35% of Australians aged 70 and older have MCI [1], and 15% of those individuals will go on to develop dementia within a year [2]. Currently, there are no approved treatment options for MCI, and evidence on anti-dementia pharmaceuticals does not support their use in people with MCI [3–5]. Sailuotong (SLT) is a novel, standardised herbal medicine preparation that has been specifically designed to target the complex pathophysiologies of vascular dementia and Alzheimer’s disease. This project will evaluate the efficacy, safety, and the mechanisms of action SLT for MCI in a 12-week randomised, double-blind, placebo-controlled pilot trial.

### MCI characteristics

MCI is a heterogeneous syndrome that is associated with an increased risk of dementia. People with MCI demonstrate objective cognitive decline but have relatively intact activities of daily living. Not all people with MCI will go on to develop dementia, and considerable efforts have been made to establish clinical phenotypes that may represent the prodromal phase for different types of dementia and to provide clinical utility in determining risk [6, 7]. MCI can be classified into clinical subtypes across two broad categories:Amnestic MCI, where some form of memory impairment is presentNon-amnestic MCI, where there is impairment in non-memory domain(s).

These classifications can be further divided into single- or multiple-domain impairments [8], where one or more cognitive domains are affected. The most common subtype, amnestic MCI, is considered the prodromal phase for Alzheimer’s disease [9], the most frequent cause of dementia. Furthermore, population studies also suggest that individuals with multiple-domain amnestic subtype MCI are most at risk of developing dementia [2].

There is no consensus on one set of diagnostic guidelines for MCI. Clinical categorisations of MCI include the Diagnostic and Statistical Manual of Mental Disorders, 4th Edition (DSM-IV) classification of Cognitive Disorder Not Otherwise Specified [10], the Petersen criteria [6], the joint National Institute on Aging-Alzheimer’s Association (NIA-AA) criteria for MCI due to Alzheimer’s disease [11], and the recent addition to the DSM-V: Mild Neurocognitive Disorder [12]. No clear cut-off scores or instruments are defined in any of these guidelines, making these criteria difficult to apply in a research setting. Instead, it is recommended that a clinical diagnosis of amnestic MCI is made (taking into account a range of evidence including both subjective and objective decline) [6, 8], as outlined in the core clinical criteria for MCI due to Alzheimer’s disease from the NIA-AA working groups guidelines [11].

### Limitations of current treatment strategies for MCI

Multiple mechanisms are thought to be involved in the pathophysiology of MCI (which is thought to be due to the early signs of Alzheimer’s disease), including chronic inflammation, anti-oxidant depletion, neurotransmitter dysfunctions (e.g. cholinergic hypofunction), and cerebral hypoxia, that can play a role in the biochemical cascade leading to increased amyloid-β production, mitochondrial dysfunction, and free radical generation [13–17].

Currently, there are no approved therapeutic agents for MCI by the US Federal Drug Administration (FDA) that may manage symptoms in the short term or prevent/slow the conversion of MCI to Alzheimer’s disease in the long term [18]. Standard clinical management of MCI involves monitoring of risk factors and cognitive decline. Pharmaceutical intervention is possible once a diagnosis of dementia is certain, and it then focuses on symptomatic management and decreasing the rate of deterioration. Cholinesterase inhibitors (donepezil, galantamine, and rivastigmine) and glutamate receptor antagonists (memantine) are the most common classes of pharmaceuticals used for Alzheimer’s disease; however, evidence of their efficacy and safety for MCI is poor and inconsistent.

The very first large-scale donepezil trial on MCI (in combination with vitamin E) observed a slower rate of progression to Alzheimer’s disease during the first 12 months, but at the 36 month follow-up, there was no difference in conversion rate between treatment groups and placebo [3]. A very large 2-year trial showed that treatment with galantamine did not differ from placebo in the conversion rate of MCI to dementia [4]. Although there were some small treatment-related improvements in cognition after 12–24 months, there was also a significantly higher mortality rate, suggesting that galantamine is not safe for individuals with MCI. A 4-year trial of rivastigmine for MCI showed no difference in dementia conversion rates and cognitive performance between treatment and placebo, with side effects including nausea, vomiting, diarrhoea, and dizziness also being reported in the treatment group [5]. There are no robust, fully powered trials on memantine for MCI [19, 20]; however, it has been suggested that there is limited evidence to support such an attempt [21]. The findings from the early trials outlined above have also been confirmed by a meta-analysis which found no effect of donepezil, rivastigmine, galantamine, or memantine on cognition or function in patients with MCI, but rather found an increased risk of nausea, diarrhoea, and vomiting compared to placebo [18].

In summary, the existing evidence to support the efficacy of anti-dementia pharmaceuticals in MCI is relatively weak. The benefits of these interventions for MCI require validation, particularly in light of the long-term management of symptoms required for patients and the risk of adverse side effects [18]. Furthermore, conventional pharmaceutical treatments typically act on a single pharmacological target and do not address the multiple pathological components of MCI as a whole. Taken together, these findings indicate that new treatments should achieve all of the following:Address the pathophysiology of MCI through a multi-target approachImprove and/or stabilise cognitive deficitsSafely manage symptoms in the long term.

### Multi-system/multi-target approach of an herbal formula for MCI

The use of herbal medicine for ageing-related disorders and longevity was documented in the literature more than 2000 years ago in ancient China. Combination therapy underpins the philosophy of Chinese herbal medicine, where patients are typically treated with multi-herbal formulations. Evidence suggests that a number of medicinal herbs, including *Ginkgo biloba* (ginkgo), *Panax ginseng* (ginseng), and *Crocus sativus* (saffron), may aid in the treatment of cognitive impairment [22]. This led to the development of a three-herb formula, Sailuotong (SLT; previously known as Wei Nao Kang, WNK), by a combined team based at Xiyuan Hospital, China Academy of Chinese Medical Sciences, China and the National Institute of Complementary Medicine (NICM), Western Sydney University, Australia. The SLT formula consists of specific dosages of standardised ginkgo, ginseng, and saffron extracts, designed for the management of cognitive impairments. The data from a series of preclinical and clinical studies show that SLT can affect multiple therapeutic targets associated with MCI and dementia [23].

### SLT formulation background

SLT represents a new generation of herbal formulations for which the chemical and pharmacological profiles have been clearly defined using analytical chemistry, pharmacognosy, and pharmacology techniques. The preclinical research contributing to the development and standardisation of SLT [23–30], the mechanisms of action of the three herbs [23, 31–38], and findings from clinical studies [22, 39–48] have all been described thoroughly elsewhere and summarised in a recent review by Chang et al. [23]. Table 1 details the multiple pharmacological targets that the active components in SLT address relevant to the pathophysiology of MCI.

**Table 1 Tab1:** Multi-target mechanisms underlying pharmacological effects of SLT components

Pharmacological effects relevant to MCI	Ginseng	Ginkgo	Saffron
Anti-inflammatory	✓	✓	✓
Anti-oxidant	✓	✓	✓
Anti-apoptotic	✓	✓	✓
Increasing cerebral blood flow		✓	
Anti-platelet aggregation		✓	
Antagonising amyloid-β accumulation	✓		
Enhancement of cholinergic function	✓		
Anti-depressant/anti-anxiety		✓	✓

### Rationale for the current project

Dementia is the single greatest cause of disability in Australians aged 65 years and older, is the second leading cause of death in Australia [49], and currently has no cure. There are more than 413,106 Australians living with dementia, and this figure is expected to rise to more than 1,100,890 by 2056 without medical breakthrough [50]. MCI, a syndrome associated with a significantly increased risk of dementia, is a growing health concern for seniors, with up to 80% of patients with MCI developing dementia within 6 years [51].

Evidence on the efficacy and safety supporting the use of anti-dementia drugs in MCI is lacking. Furthermore, these treatments have focused on single therapeutic targets such as cholinesterase or glutamate which do not adequately address the complex and multi-system nature of MCI. SLT, however, consists of multiple bioactive components addressing different pathophysiological causes of cognitive impairments through various pharmacological activities that reduce inflammation, oxidative stress, and apoptosis; inhibit platelet aggregation; and increase blood flow, anti-oxidant capacity, and brain tissue acetylcholine (ACh) concentrations (see Table 1). Preclinical work and pilot clinical trials have provided convincing evidence on the beneficial effects of SLT in various animal models in healthy adults, and in people with vascular dementia. Together, this suggests that SLT can potentially provide a viable intervention for the management of MCI. A clinical trial with a rigorous design is needed to confirm the efficacy of SLT on cognitive function, its mechanisms of action, and its safety in an MCI cohort.

## Methods/design

### Study design, ethics, and setting

The study design is a randomised, double-blind, placebo-controlled trial. Information on the testing schedule and the outcome measures is detailed further below. Ethics approval was requested and approved through the Western Sydney University Human Research Ethics Committee (Approval H11878). The trial was registered with the Australian New Zealand Clinical Trials Registry (ACTRN12617000371392) on 10 March 2017. The current study protocol (version 3) was designed in accordance with Standard Protocol Items: Recommendations for Interventional Trials (SPIRIT) [52] (see Additional file 1) and Good Clinical Practice guidelines (1996). Any changes to the study protocol will be communicated with the study investigative team, the Australian New Zealand Clinical Trials Registry, and the approving ethics committee. The study is being conducted in the NICM Clinical Laboratory and HEADBOX Lab at Western Sydney University, Campbelltown campus.

### Study aims

The primary aim of this project is to evaluate the efficacy of 12 weeks of SLT (compared with placebo) on cognition in people with MCI. The secondary aims of this study are to 1. assess the mechanisms of action of SLT via electroencephalography (EEG), autonomic function, cerebral blood flow, and inflammation, and 2. evaluate the safety of SLT.

### Intervention

#### SLT treatment

The SLT formula is standardised by 10 bioactive components of the three herbal extracts from *Panax ginseng*, *Ginkgo biloba*, and *Crocus sativa*. A range of in vivo pharmacological studies have been undertaken to test the bioactivity and determine the optimal ratio of the three individual herbal extracts. Each SLT capsule contains a 45-mg standardised mixture of 20.46 mg ginsenosides from *Panax ginseng*, 20.46 mg total ginkgo flavone glycosides from *Ginkgo biloba*, and 4.09 mg crocins from *Crocus sativa*. The SLT preparations have been manufactured in a Good Manufacturing Practice facility certified by the Australian Therapeutic Goods Administration. The dose is 180 mg (4 × 45-mg capsules, 2 in the morning and 2 at night) of SLT per day for 12 weeks.

#### Placebo

The placebo consists of 4 capsules per day (2 each morning and night), containing an inert substance (starch filler, silica coating, with taste and colouring added) matched for the colour, taste, and smell of SLT.

### Recruitment, consent, and reimbursement

A number of avenues are being pursued for recruitment. Advertisements will be placed in local papers in surrounding areas; flyers will be placed around local community centres and residential aged care facilities as well as Western Sydney University campuses. Internet advertisements will be placed on several websites including those for Western Sydney University, NICM, Alzheimer’s Australia, the Dementia Research Foundation, and the Dementia Collaborative Research Centres. Advertisements will also be placed in university newsletters and at other external organisations such as Illawarra Retirement Trust (IRT) where possible. The study will also be promoted through social media including Twitter and Facebook. A link to the study’s screening page will be included in all online recruitment pathways. Participants will be directed to complete the online screening form, and their contact details will be collected. Local general practitioner (GP)/specialist clinics will be contacted and encouraged to identify and refer suitable MCI patients to this study. Potentially eligible participants from other studies in our laboratory will also be invited to participate in this trial.

Written information on the study will be provided, and participants will have the opportunity to verbally discuss the study with the research team. At a face-to-face screening, the participant and his informant will each sign an informed consent form.

Participants will be offered reimbursement to cover travel expenses for their study visits: up to $30/visit will be provided. Each participant will complete 6 visits (1 × screening, 2 × baseline, 1 × midpoint, 2 × endpoint), totalling up to $180. Parking will be provided free of charge at Western Sydney University’s Campbelltown campus.

### Inclusion/exclusion criteria

Participants will be assessed against the following inclusion criteria:≥ 60 years of ageNo diagnosis of dementiaConfirmed diagnosis of MCI due to Alzheimer’s disease core clinical criteria according to the NIA-AA working group guidelines [11]No severe depression: scoring ≤19 on the 30-item Geriatric Depression Scale (GDS)Agreement to provide informed consent.

They will also be assessed for the following exclusion criteria:Diagnosed psychiatric disorders including dissociative disorder, obsessive-compulsive disorder, personality disorders, schizophrenia, bipolar disorderHistory of drug and alcohol dependence or substance-related disordersHistory of seizuresHead trauma with loss of consciousnessLeft-handedness (for EEG testing)Allergic to at least one ingredient of SLTCurrent use of ginkgo, ginseng, or saffron○ Participants taking these herbal medicines will be asked to cease use for an 8-week washout period prior to participation in the trialHistory of severe renal and hepatic disorders.

### Sample size

There are no similar studies using SLT for the proposed study duration (12 weeks) in an MCI cohort. Thus, we selected a well-designed study that used the same primary outcome measure and a similar cohort with a 16-week intervention. That study also provided effect sizes at midpoint (8 weeks) [53]. Craft et al. [53] demonstrated significantly improved delayed recall scores on the Logical Memory Story A subtest of the Wechsler Memory Scale, 4th Edition (WMS-IV) following 8 weeks of 20 IU insulin: a treatment group × time interaction, *p* = 0.020, Cohen’s *f* = 0.36.

We utilised this effect size to conduct an a priori sample size calculation based on the Logical Memory Story A subtest of the WMS-IV. To detect an effect size of Cohen’s *f* = 0.36 at α = 0.05 and 80% power, 63 participants across two groups are required. Allowing for a 20% dropout, this means that 76 participants (38 per group) are required; we rounded this to 80 participants to facilitate a permuted block randomisation strategy. Note also that because this study is a pilot efficacy study (phase II), a larger sample size to reach a higher degree of statistical power is not required.

### Assessments and testing schedule

A schematic of the trial protocol is detailed in Fig. 1. Eligible participants will be screened via telephone (45 min) and invited to attend a face-to-face screening session (1.5–2 h) where informed consent and verification of safety to participate (via commercial laboratory blood test) will be obtained. Once enrolled in the study, participants will be randomly allocated to either the treatment or placebo condition. Two testing sessions (cognitive and physiological) will be conducted at baseline and at endpoint over 2 separate days (3–4 h each); the midpoint assessment will be conducted on a single day (30 min). The schedule of assessments is detailed in Fig. 2.

**Fig. 1 Fig1:**
[figure not shown]
Schematic of participant flow

**Fig. 2 Fig2:**
[figure not shown]
Schedule of interventions and assessments at screening (phone and face-to-face), baseline, midpoint, and endpoint sessions

### Screening assessment

#### Phone screen

Participants will undergo an initial telephone interview assessing them against the study’s inclusion and exclusion criteria and estimating cognitive function and decline using the 13-item modified Telephone Interview for Cognitive Status (TICS-M) and Test of Premorbid Functioning (ToPF), respectively.

#### Face-to-face screen

After written informed consent is obtained from both the participant and her informant, the participant’s medical history and demographics will be taken with a semi-structured clinical interview, and the participant will be assessed against the NIA-AA core clinical criteria for MCI due to Alzheimer’s disease [11] using the Informant Questionnaire on Cognitive Decline in the Elderly (IQCODE) [54], the Montreal Cognitive Assessment (MoCA) [55], the Pfeffer Functional Activities Questionnaire (FAQ), the GDS [56, 57], and the Rey Auditory Verbal Learning Test (RAVLT). The various screening instruments, their purpose, and administration method are summarised in Table 2.

**Table 2 Tab2:** List of items used during screening, their purpose, and administration method

Task	Purpose	Administration method
TICS-M	Screen for cognitive informant	Test: participant and informant
ToPF	Level of functioning prior to cognitive decline	Survey: participant
Pfeffer FAQ	Activities of daily living	Survey: informant
IQCODE	Informant questionnaire to corroborate cognitive difficulties	Survey: informant
MoCA	Screen for MCI	Test: participant
RAVLT	Objective memory impairment	Test: participant
Medical history	General health and functioning	Interview: participant and informant
GDS	Depression screen	Survey: participant

*Abbreviations: TICS-M* Telephone Interview for Cognitive Status-Modified, *ToPF* Test of Premorbid Functioning, *Pfeffer FAQ* Pfeffer Functional Activities Questionnaire, *IQCODE* Informant Questionnaire on Cognitive Decline in the Elderly, *MoCA* Montreal Cognitive Assessment, *RAVLT* Rey Auditory Verbal Learning Test, *GDS* Geriatric Depression Scale

### Primary outcome measures

There are four co-primary outcome measures:Logical Memory Story ADigit Symbol CodingDelis-Kaplan Executive Function System (D-KEFS) Trail Making Test Condition 4Rey Complex Figure Test.

People living with multiple-domain amnestic subtype MCI^1^ showing deficits in episodic memory, executive function, and perceptual processing speed are particularly at risk of progressing to Alzheimer’s disease [58]. Episodic memory is the most reliable predictor of this conversion [58]; thus, an appropriate and widely used episodic memory measure (Logical Memory Story A) was selected for the sample size calculation. The other three co-primary outcome measures were selected due to their relevance in testing the other domains: Digit Symbol Coding measures perceptual processing speed, and the D-KEFS Trail Making Test Condition 4 and the Rey Complex Figure Test measure executive function.

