### Statistical analyses and data management

The study will largely employ a mixed-model design with a between-subjects factor of group (treatment vs. placebo) and within-subjects factor of time (baseline vs. endpoint). Analyses of variance (ANOVAs) will be conducted to assess differences in continuous outcome measures between the two groups. All tests will be one tailed, α = 0.05. As there are only two testing points for the primary outcome measures (baseline and endpoint), data from any participants failing to complete follow-up will not be included in the final analysis.

All data will be stored on a secure server with two back-up copies on external hard drives. Paper-based forms will be digitised and the original copies stored in locked filing cabinets in secure rooms that require swipe card access at Western Sydney University Campbelltown campus. All participants are de-identified upon randomisation and referred to on all forms with a participant ID. A password-protected spreadsheet stored on the secure server links participant names to ID codes to all for re-identification to occur if required. As this is a relatively small investigator-initiated pilot trial, a data monitoring committee and auditing process are not required.

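### Four co-primary outcomes are each tested at an unadjusted one-tailed 0.05 with no success rule, and the 80% power covers only Logical Memory Story A

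*Protocol article*

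**What the plan says.** Under Primary outcome measures the protocol article says "There are four co-primary outcome measures": Logical Memory Story A, Digit Symbol Coding, D-KEFS Trail Making Test Condition 4 and the Rey Complex Figure Test. The same section explains that "an appropriate and widely used episodic memory measure (Logical Memory Story A) was selected for the sample size calculation", and that the other three were chosen to cover further cognitive domains.

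Sample size uses an "effect size of Cohen’s *f* = 0.36 at α = 0.05 and 80% power" and concludes that "63 participants across two groups are required". Allowance for 20% dropout and rounding bring enrolment to 80.

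Statistical analyses and data management fixes the threshold: "All tests will be one tailed, α = 0.05". It also restricts the analysis to participants who complete follow-up.

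The Discussion paragraph of the Abstract says that the data "will inform a larger, more highly powered clinical trial if the findings are positive". The article does not define a positive finding. It gives no alpha split, no testing order and no statement of how many of the four outcomes must succeed.

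**The concern.** With four primary tests, the error rate and the power of the trial's main conclusion depend on the rule that combines them. If one significant result is enough, testing each at the full 0.05 raises the chance of a false positive conclusion well above 5%. If all four must be significant, which is the usual meaning of co-primary, no alpha adjustment is needed, but the relevant power is the joint power, and the sample size does not address it.

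This is more than detail left to an analysis plan. The article itself declares four primaries and assigns 0.05 to every test, so a plan that adjusted alpha would depart from the published text. The primary aim is efficacy and the result is meant to inform a larger trial, so readers need to know what a positive result is and how often it would arise by chance.

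**Working it through.** **Inputs.** From the article: four co-primary outcomes; one-tailed alpha 0.05 for each test; f = 0.36, alpha 0.05 and 80% power for Logical Memory; 63 evaluable; 80 enrolled at 1:1; 20% dropout; completers only. Assumed, because the article gives no figure: equal correlations between the four test statistics (0 to 0.9) and, where needed, f = 0.36 on the other three outcomes as well.

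**Step 1. Reproduce the sample size.** For two groups d = 2f = 0.72. In the two-group F test the noncentrality is f²N = 0.1296 × 63 = 8.16. Power is 0.803 at N = 63 and 0.797 at N = 62, so 63 is reproduced exactly, for one outcome. The F test corresponds to a two-sided t test. Dropout: 63 × 1.2 = 75.6, which gives the stated 76. Completers expected from 80 enrolled: 80 × 0.8 = 64.

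**Step 2. Power on Logical Memory as the analysis is planned.** One-sided t test at 0.05 with 64 completers and noncentrality f√N = 0.36 × 8 = 2.88: power 0.886 (0.881 at 63).

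**Step 3. Any one of four counts.** For independent tests, the chance of at least one false positive is 1 − 0.95⁴ = 0.185. The correlated cases come from simulating 1,000,000 equicorrelated normal vectors:

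| Assumed correlation | At least one false positive |
|---|---|
| 0 | 18.5% |
| 0.3 | 16.3% |
| 0.5 | 14.4% |
| 0.7 | 12.0% |
| 0.9 | 8.8% |

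**Step 4. All four must succeed.** Family-wise error is at most 5% without adjustment. Joint power uses f = 0.36 on all four, 64 completers and one-tailed 0.05. Independent tests: 0.886⁴ = 0.62. Normal simulation for correlated tests: 68% at 0.3, 72% at 0.5, 77% at 0.7, 79% at 0.8 and 82% at 0.9. Simulating the t tests directly gives results about one point lower. If the other three outcomes had f = 0.25 to 0.30 (assumed), joint power would be about 33% to 55% at correlations 0.3 to 0.5.

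**Step 5. What control of the error would cost on Logical Memory (64 completers, one-sided).**
- Bonferroni, 0.05/4 = 0.0125 each: 71.9%. Reaching 80% would need 76 completers, or 76/0.8 = 95 enrolled.
- Holm across all four, with f = 0.36 on each: about 84%, 83%, 82%, 80% and 79% at correlations 0, 0.3, 0.5, 0.7 and 0.9. It falls towards the Bonferroni 72% if the other three have no effect.
- Logical Memory tested first at the full 0.05, the others only if it succeeds: 88.6%, with family-wise error held at 5%.

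**The case against.** The strongest reply is that nothing the article claims is contradicted. The 80% is given for Logical Memory, and joint power is never promised. Under an all-four rule the error is controlled and Logical Memory's own power is about 88% at one-tailed 0.05. This is also a phase II pilot, and an article need not set out every detail of a multiple-testing procedure.

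Much of this stands, and it rules out several stronger readings that a reader might infer:

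- *The trial cannot have both a 5% error rate and its stated power.* It can. Logical Memory first in order keeps about 88%. Holm keeps about 79% to 84% if all four effects equal f = 0.36. With no dropout, one-sided Bonferroni at 80 completers gives 82%.
- *One nominal success counts as efficacy.* The article does not say so. It leaves the rule open.
- *A positive result triggers the next trial.* The text says that the data will inform it, and sets no go/no-go threshold.
- *Joint power is 41% to 62%, or Bonferroni power is 62%.* The first range assumes 80% power per test (0.80⁴ = 0.41 if independent), and the second figure uses a two-sided 0.0125. Neither is the plan's one-tailed 0.05.
- *Unnamed scores mean more than four primary tests.* The Abstract names delayed recall for Logical Memory, and the choice of Rey score is detail that an article may leave to fuller documents.

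The pilot label does not remove what is left. The remark under Sample size excuses limited power and is silent on false positives.

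**Conclusion.** The concern holds in a limited form. Four co-primary outcomes share an unadjusted one-tailed 0.05, only one of them is powered, and no success rule is stated, so neither family-wise error nor power for the overall conclusion is fixed. If any one success counts, the false-positive rate is about 9% to 19% (18.5% under independence). If all four are needed, error is controlled but joint power is about 62% to 77% for correlations 0 to 0.7, and reaches 80% only above roughly 0.8. The correlations are assumed, and an f of 0.36 on the three unpowered outcomes is a generous assumption for which the article gives no support. The defect lies in the missing rule, and it can be repaired at the planned sample size.

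**What to change.** State in the protocol how many of the four outcomes must succeed, and control family-wise error across them. The preferred form is to test Logical Memory Story A delayed recall first at the full alpha and, only if it succeeds, the other three in a fixed order or by Holm. Holm across all four is an acceptable alternative. State that the 80% power refers to Logical Memory alone, and define a positive finding in the Abstract by the same rule.

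The cost is protocol and registry wording before unblinding, with no added participants. The small downside is that the other three outcomes may go formally untested if the first fails. They need not lose co-primary status, and a change to two-sided testing is not needed for this repair.

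Two separate points should be reconciled in their own right: the sample size is a two-sided figure while the analysis is one-tailed, and the Abstract lists Letter Number Sequencing where Primary outcome measures lists Digit Symbol Coding.
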